**Fig. 2 Fig2:**
[figure not shown]
Flow diagram of the study protocol

### Study participants and eligibility criteria

The study will include outpatients of the Geriatrics Department of the Complejo Hospitalario of Navarra, the Matia Foundazioa in San Sebastian and the Hospital of Getafe (all three in Spain) older than 75 years of age between September 2017 and May 2019. Inclusion criteria include patients aged 75 years or older being capable and willing to provide informed consent, able to communicate and ambulate with or without personal/technical assistance, with a Barthel Index ≥ 60 and MCI or mild dementia according to DSM V criteria [31], level GDS-4 (Reisberg classification) [32], pre-frail or frail according to the Fried criteria [4] and having someone to help to supervise them when conducting the exercises.

The exclusion criteria include having any factor that precludes the performance of the physical training programme or testing procedures as determined by the attending physician. These factors, according to the VIVIFRAIL programme [26] include, but are not limited to, the following:myocardial infarction in the past 3 months;unstable angina pectoris;terminal illness;uncontrolled arrhythmia;unstable cardiovascular disease or other unstable medical condition;uncontrolled arterial hypertension;recent pulmonary thromboembolism;upper or lower extremity fracture in the past 3 months;institutionalized or pending entry into institution; andunwillingness to either complete the study requirements or to be randomized into the control or the intervention group.

### Randomization and blinding

Participants in the study will be randomized (www.randomizer.org) into an intervention group and a usual care group (control group) following a simple randomization procedure, in a 1:1 ratio without restriction. Participants will be explicitly informed and reminded not to discuss their randomization assignment with the assessment staff. The assessment staff will be blinded to the participants’ groups as well as to the main study design and to what changes in study outcomes we expect to occur in either group.

It will not be possible to conceal the group assignment from the staff involved in the training of the intervention group. Patients (or their families) will be informed of their random inclusion in one group but will not be informed regarding to which group they belong.

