## Methods

### Study design and setting

This study is a multicentre randomized clinical trial to be conducted in the outpatient geriatrics clinics of three tertiary hospitals in Spain. Geriatric clinics are part of routine geriatric clinical work and normally patients come from primary care or other specialities. Patients who meet the inclusion criteria will be randomly assigned to the intervention or control group. Prior to randomization, the attending geriatrician will review the absolute and relative contraindications to participate in the exercise programme and will provide general information about the study. Patient recruitment will begin with the normal visit of the patient to the clinic assessing for inclusion criteria and obtaining informed consent. Later on, subjects will be randomly assigned (as explained in the following) to either the intervention or the control group. The researcher who decides whether the patient is assigned to the intervention or control group will not be the attending geriatrician. Patients or their relatives (if the patient has dementia) will be informed of the random inclusion in one group but will not be informed regarding to which group they belong. The data for both the intervention group and the control group will be obtained at three different times: at baseline and at the 1-month and 3-month follow-up. We will perform two telephone calls (15 days and 2 months after baseline) to assess adherence and reinforce the protocol applied. In addition, in order to improve the adherence of the exercise programme, participants in the intervention group will record a diary that will be reviewed during follow-up. After randomization, the research team (physiotherapist, sport science specialist and geriatrician) will together perform the baseline measurement and follow-up visits of functional, pharmacological, comorbidity and cognitive assessment, as well as of mobility and strength evaluations (Table 1). The multidisciplinary research team have well-known previous experience in functional geriatric assessment and in the prescription of exercise in frail aged participants in different clinical settings [25, 26, 28].

**Table 1 Tab1:** Schedule for the different primary and secondary variables for the participants of the study

Measure	Screening	T1 Baseline	T2 1 month	T3 3 months
Primary outcome				
Short Physical Performance Battery (SPPB)		X	X	X
Secondary outcomes				
Barthel Index	X		X	X

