### Statistics and sample size

Assuming an alpha error of α = 5%, a correlation between pre and post-intervention values of the Short Physical Performance Battery (SPPB) of ρ = 0.5 and a standard deviation for the SPPB of σ = 2.5, the required sample size to have a power of 90% to detect a minimum difference of 1 point between groups in the post–pre SPPB score is 101 patients per group. Taking into account an expected loss of patients along the follow-up of 15%, the final sample size required is 120 per group. For the estimation, an ANCOVA method for the analysis of the differences has been considered. The research team will be focused to instruct and remind geriatricians periodically to assess inclusion and exclusion criteria in all three centres in order to reach target sample size. All of the centres have a remarkable clinical activity attending around 1000 patients every year. It is expected than 15% of these patients in every centre can be potentially eligible participants. In the unlikely case of not reaching the expected sample size, we will extend the inclusion period for a further 3 months.

The description of the sample by group will be conducted using statistics such as means and standard deviations or medians and interquartile ranges for the quantitative variables, and frequencies and percentages for the qualitative variables. For comparisons between groups at baseline, *t* tests or Mann–Whitney *U* tests will be used for continuous variables, depending on normality, which will be checked for each using the Kolmogorov–Smirnov test and normal probability plots, and the chi-square test or Fisher’s test will be used for categorical variables. To determine the efficacy of the intervention in the quantitative variables, such as the SPPB, we will use ANCOVA models, using post-intervention values as dependent variables, group study as the principal effect and pre-intervention values as covariates. In the case of qualitative or categorized variables (such as whether an improvement of a given magnitude between pre and post intervention has been achieved or not), comparisons between groups will be conducted with the chi-square test or Fisher’s test, and complemented with logistic regression if additional adjustment is needed. The level of statistical significance will be 0.05. Data will be analysed using an intention-to-treat approach with R and SPSS statistical packages.

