#### Secondary outcomes

Loss of handgrip in the dominant hand is a useful tool for the measurement of functional capacity. This characteristic is a strong predictor of disability, morbidity and mortality as well as one of the components of Fried’s frailty phenotype [4]. Furthermore, the functional status of patients will also be assessed at recruitment with the Barthel Index [37], an international and validated tool of disability. The score ranges from 0 (severe functional dependence) to 100 (functional independence). At baseline, gait ability will be assessed using the 6-m gait velocity test (GVT). Starting and ending limits will be marked on the floor with tapelines for a total distance of 8 m. Participants will be instructed to walk at their self-selected usual pace for two attempts. The best result of both trials will be registered. The first and last metre, considered the warm-up and deceleration phases, respectively, will not be included in calculations of the gait assessment. Dual-task conditions (gait evaluation during the simultaneous performance of a cognitive task) have recently been recognized as a sensitive assessment method for interactions among cognition, gait, falls and frailty. Changes in gait parameters (i.e. gait velocity and gait variability) while performing a dual-task test (dual-task cost) may be early predictors of fall risk [38, 39] and may be useful tools for functional evaluations in frail older patients. Exercise can modify the dual-task cost and, consequently, the fall risk and functional capacity [40]. The dual-task paradigm [37] will be used in the 6-m habitual GVT. Two trials will be conducted to assess gait velocity while the patient is performing a verbal or counting task (verbal GVT and arithmetic GVT, respectively). During the verbal dual-task condition (verbal GVT), we will measure gait velocity while participants are naming animals aloud. During the arithmetic dual-task condition (arithmetic GVT), we will assess gait velocity while participants are counting backwards aloud from 100 in ones. The cognitive score will be measured by counting the number of animals named (dual-task with verbal performance) or determining how many numbers were counted backwards (dual-task with arithmetic performance). Isometric upper limb (dominant hand grip) and lower limb (right knee extensors and hip flexors) muscle strength will be measured using a manual dynamometer. Maximal dynamic strength will be assessed using the 1RM test in the bilateral leg press exercise using exercise machines (Matrix, Johnson Health Tech, Ibérica, S.L., Torrejón de Ardoz, Spain; and Exercycle S.L., BH Group, Vitoria, Spain). In the first assessment, the subjects will warm up with specific movements for the exercise test. Each subject’s maximal load will be determined in no more than five attempts, with a 3-min recovery period between attempts. After the 1RM values are determined, the subjects will perform 10 repetitions at maximal velocity and at intensities of 50% of 1RM to determine the maximum power (W) and the loss of power during the 10 repetitions in the leg press exercise [41]. The power will be recorded by connecting a velocity transducer to the weight plates (T-Force System, Ergotech, Murcia, Spain). During all neuromuscular performance tests, strong verbal encouragement will be given to each subject to motivate them to perform each test action as optimally and rapidly as possible. Distribution of the training sessions throughout the day should minimize cumulative fatigue and help to maintain adherence. Adherence to the exercise programme will be documented in an individual daily log of the sessions. Changes in cognitive-affective status after the intervention will be measured using the Spanish validated versions of the Minimental Cognitive Exam (MEC-Lobo) [42] in the case of dementia and the MOCA [43] in the case of MCI. The Yesavage GDS [44] and Trail Making part A [45] will be performed to assess depression and executive dysfunction. During functional tasks (such as balance, gait and rising from a chair) and cognitive evaluations (dual tasking), an inertial sensor unit (IU) will be attached over the lumbar spine (L3) to record the acceleration data in control and intervention participants [46, 47]. Primary and secondary variables are presented in Table 1.

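### Centre and diagnosis are neither balanced by the randomization nor adjusted for in the ANCOVA: the analysis stays valid, but cheap precision and protection against chance imbalance are forgone

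*Protocol article*

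**What the plan says.** All references are to the protocol article.

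- *Study design and setting*: the trial runs in the "outpatient geriatrics clinics of three tertiary hospitals in Spain".
- *Study participants and eligibility criteria*: patients have "MCI or mild dementia according to DSM V criteria". Diagnosis is therefore known before allocation.
- *Randomization and blinding*: allocation is made "following a simple randomization procedure, in a 1:1 ratio without restriction". There are no blocks and no strata.
- *Statistics and sample size*: quantitative outcomes, including the SPPB, are analysed by ANCOVA, "using post-intervention values as dependent variables, group study as the principal effect and pre-intervention values as covariates". Neither centre nor diagnosis is a term.
- The same section compares categorical outcomes by chi-square or Fisher's test, "complemented with logistic regression if additional adjustment is needed". No covariates are named, and nothing says what would make adjustment necessary.
- *Secondary outcomes*: diagnosis also decides the cognitive instrument. The MEC-Lobo is used "in the case of dementia and the MOCA" in the case of MCI.

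**The concern.** Centre and diagnosis are recorded for every patient before allocation, and either could predict 3-month SPPB beyond what baseline SPPB already predicts. The design leaves their balance to chance and the stated model does not correct for them. Because the model's terms are written out, this is a stated choice and not a detail left to a later analysis plan.

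Two things are at stake. In the one trial that is actually run, the estimate can be shifted by a centre or diagnosis imbalance that could have been adjusted away. And any residual variance that the two factors explain stays in the standard error.

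**Working it through.** **Inputs from *Statistics and sample size*:** alpha 0.05 (taken as two-sided), power 90%, difference 1 SPPB point, SD 2.5, pre–post correlation 0.5, 101 per group, 15% loss, 120 per group. The article gives no centre sizes, no MCI/dementia split and no prognostic strength for either factor. Those are assumptions below, shown with ranges.

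**1. The plan's own figure**
- Residual SD under ANCOVA = 2.5 × √(1 − 0.5²) = 2.165.
- n per group = 2 × 2.165² × (1.960 + 1.282)² / 1² = 98.5, so 99. The noncentral-t version with one covariate gives 100. The stated 101 reproduces within 2 patients.
- 101 / 0.85 = 118.8, so 119, against the stated 120. Conversely, 120 × 0.85 = 102 analysed per arm.

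The calculation does not rely on centre or diagnosis.

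**2. Chance imbalance by centre**

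The number in one arm of a centre of size n is Binomial(n, 0.5).
- n = 80: P(48:32 or worse) = 0.093. For at least one of three centres: 1 − (1 − 0.093)³ = 0.254.
- If the centres were 120, 80 and 40, the 60/40-or-worse probabilities are 0.035, 0.093 and 0.268. For at least one: 1 − 0.965 × 0.907 × 0.732 = 0.36.

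**3. Chance imbalance by diagnosis**

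MCI and dementia patients split independently under simple randomization. If a and b are the MCI and dementia counts in one arm, the gap in MCI share is a/(a+b) − (120−a)/(240−a−b), with a and b each Binomial(120, 0.5). Summing exactly:
- P(gap of 10 percentage points or more) = 0.137. With 60 patients in one diagnosis and 180 in the other it is 0.080.
- The SD of the gap is 0.065.
- P(gap of 16.7 points or more) = 0.012.

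The shift in the estimate is the gap times the prognostic difference left after baseline adjustment. For a 10-point gap:

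| Residual difference (assumed) | Shift in estimate | Share of residual variance at a 50/50 split (d² × 0.25 / 2.165²) |
|---|---|---|
| 0.5 points | 0.05 | 1.3% |
| 1.0 points | 0.10 | 5.3% |
| 1.5 points | 0.15 | 12% |

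**4. Precision**

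Let f be the share of residual variance explained by centre and diagnosis together. The residual SD becomes 2.165 × √(1 − f). Noncentral-t power at 102 per arm, after spending the 3 extra degrees of freedom:

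| f (assumed) | Power | SE relative to stated model |
|---|---|---|
| 0 | 90.7% | 1.000 |
| 0.03 | 91.5% | 0.985 |
| 0.05 | 92.0% | 0.975 |
| 0.10 | 93.3% | 0.949 |

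The stated model also gives 90.7%, so at f = 0 the cost is negligible. At f = 0.10 the gain equals 1 / 0.90 = 1.11, or 11% more patients.

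**5. Cognitive outcomes**

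If the MCI group has 120 patients (assumed), the 95% range for the number in one arm is 49 to 71. An instrument used in one diagnosis only is analysed in arms whose sizes are left to chance.

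**The case against.** The strongest reply is that nothing here is wrong. Simple randomization with the stated ANCOVA is unbiased on average and holds its type I error, and chance imbalance is already reflected in the standard error. The chance shift from diagnosis has an SD of about 0.065 points per point of residual prognostic difference, against a treatment-effect standard error of 2.165 × √(2/102) = 0.30. Baseline SPPB already corrects whatever imbalance acts through it. The article gives no evidence that centre or diagnosis predicts 3-month SPPB beyond that. It gives one description of usual care for the whole trial, and the two leg-press makes it names are not tied to centres and do not bear on the SPPB. All of this stands, and it keeps the point small.

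Four stronger readings are tempting but are not supported.

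- **A 70:50 split of MCI patients shifts the estimate by 0.17 points.** The split has probability 8.2%, but 70/120 − 50/120 = 0.167 also requires dementia to split 50:70 the other way. With dementia at 60:60 the gap is 70/130 − 50/110 = 0.084, or about 0.08 points per point of prognostic difference. A gap of 16.7 points or more has probability about 1.2%.
- **Covariates will be chosen from baseline p-values.** The sentence that begins "For comparisons between groups at baseline" names tests alongside the description of the sample and never says that their results select covariates. The conditional clause covers only logistic models for categorical outcomes; the SPPB ANCOVA has no conditional adjustment.
- **The plan conflicts with the CONSORT statement it cites.** That text is not in the documents, so this cannot be argued from them.
- **The trial is underpowered.** The stated sample size reproduces without either factor.

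**Conclusion.** The point holds as an optional improvement. Leaving centre and diagnosis out of both the allocation and the model is a stated choice that invalidates nothing, but it gives up a correction that costs almost nothing.

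The size is modest. A noticeable centre split is quite possible (25% with equal centres, 36% in the unequal example), but it matters only if centre is prognostic beyond baseline SPPB. For diagnosis, a gap of 10 points or more has a probability of about 8% to 14%, and a 10-point gap moves the estimate by 0.05 to 0.15 points against a target of 1. Power gains range from nil to about 2.6 percentage points (93.3 − 90.7). These figures rest on assumed centre sizes, diagnosis split and prognostic strength, and the true gain could be zero.

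**What to change.** Before unblinding, prespecify the primary model as:

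3-month SPPB ~ group + baseline SPPB + centre + diagnosis (MCI or mild dementia).

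Add the same two covariates to the secondary ANCOVA models, omitting diagnosis where an outcome is measured in only one diagnostic group. Use the same fixed set in the logistic models, in place of adjustment left to be decided as needed.

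The cost is a sentence or two of analysis text and 3 degrees of freedom (two for centre, one for diagnosis). Both variables are known for every patient, no new data are needed, and the sample size and randomization need not change.

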##### Flexibility

Sets and repetitions:◦ Two sets of three repetitions (remain in the same position for 10 s).Intensity and progression:◦ Stretch until you feel a bit of tension and then remain in the same position for 10–12 s.◦ Stretch without creating any excessive muscular elongation or articular tension.◦ Every day.◦ After the muscular strength and power or cardiovascular exercises.Flexibility exercises are shown in Izquierdo et al. [26].

Materials will be also provided to the caregivers and the participants in the Spanish language. All of the materials to be used will be properly adapted to the focused population. This exercise programme has recently launched the Vivifrail App for IOS and Android operating systems, which enables health professionals to assess the functional ability of elderly subjects and help them to prescribe a tailored multi-component physical exercise programme [26, 27] (www.vivifrail.com).

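### The protocol says patients and families are not told their group, but an exercise programme against usual care without a sham cannot be masked from them

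*Protocol article*

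**What the plan says.** Under Randomization and blinding, the protocol article closes by saying that patients or their families will learn that they were randomized but "will not be informed regarding to which group they belong". Study design and setting makes the same statement about patients or, in dementia, their relatives, who "will be informed of the random inclusion in one group but will not be informed regarding to which group they belong".

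The blinding section also contains this instruction: "Participants will be explicitly informed and reminded not to discuss their randomization assignment with the assessment staff". It describes the assessment staff as blinded to group, and it concedes that staff who train the intervention group cannot be.

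Other sections describe what participants will experience. Eligibility requires "having someone to help to supervise them when conducting the exercises". Under Study design and setting, "participants in the intervention group will record a diary that will be reviewed during follow-up". The intervention description sets a 12-week programme and adds: "Materials will be also provided to the caregivers and the participants in the Spanish language". The control arm receives ordinary outpatient care, with rehabilitation if required.

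**The concern.** The blinding section treats participants both as not knowing their group and as holding an assignment that they must not disclose. Only the second fits an exercise trial with a usual-care control.

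Who was masked decides how the outcomes may be read. EQ-5D, the depression scale and the pain scale rest on what the participant says, and adverse events are collected partly by self-report. Knowing one's arm can shift such answers. A reader who takes the sentence at face value would treat these results as coming from masked participants and give them more weight than the design supports. The protocol commits to CONSORT reporting, so the description of who was blinded needs to be accurate.

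Assessor blinding is also involved. It depends partly on participants not revealing an assignment they know. The diary is reviewed during follow-up, and both training and testing staff record adverse events, so disclosure is a realistic risk. The protocol should state plainly that participants know their group and why they must keep it to themselves.

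**Working it through.** No arithmetic settles this point. The sample-size inputs (SD 2.5, correlation 0.5, difference of 1 SPPB point, 90% power, 101 per group before losses) do not involve participant masking and do not change with the correction. The check is a comparison of the protocol's own statements.

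1. **Is the statement a single slip?** No. It appears in Study design and setting and again in Randomization and blinding.

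2. **Is it consistent with its own section?** No. The reminder not to discuss the assignment with assessors has little purpose for people who do not know it.

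3. **Do participants know what the two arms are?** Yes. The exclusion criteria under Study participants and eligibility criteria include refusal to be randomized to either control or intervention, so both options are put to candidates beforehand.

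4. **What separates the arms from the participant's side?**

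| Feature | Exercise arm | Usual care arm |
|---|---|---|
| 12-week exercise programme | yes | no |
| Adherence diary | yes | not described |
| Helper supervising the exercises | yes | no programme to supervise |
| Materials for caregivers and participants | yes, within the intervention description | not described |
| Sham or attention control | not applicable | none described |

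Having a helper is an eligibility condition for both arms, so a helper's existence reveals nothing. Supervising the exercises does, to participant and helper alike.

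5. **Who can be blinded?** The section already accepts that training staff cannot. The same reasoning applies to the people doing the exercises and to those supervising them. Outcome assessors remain, and the protocol states that they are blinded.

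6. **Which outcomes are directly affected?** Table 1 lists EQ-5D, the depression scale and a categorical pain scale. By their nature these depend on the participant's answers. Adverse events are stated to come partly from self-report. For the Barthel Index, the Functional Activities Questionnaire and falls, the article does not say who supplies the information, so they are not counted here. The primary instrument, the SPPB, is a performance test.

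**The case against.** The strongest reply is that the sentence concerns what people are told, not a claim of participant blinding. The article applies the word blinded only to the assessment staff and nowhere calls the trial double-blind. In Study design and setting the sentence sits within the recruitment and consent sequence, so it might describe disclosure at enrolment only. Some of this stands: a reader might infer that the sponsor claims a double-blind trial or labels self-reported outcomes as blinded, and the documents say neither. The enrolment-only reading is weak, however. In the second place the sentence stands under the blinding heading, directly after the remark on staff who cannot be masked.

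It can also be said that the reminder protects the assessors whether participants were told their group or worked it out. That is right, and the reminder should stay. It does not reconcile the two statements.

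A reader might go further and infer an inflated false-positive rate for the self-reported outcomes. The documents give no size for expectation bias, so any such rate would rest on a chosen value. That bias would come from participants being unblinded, which is unavoidable here, and correcting the sentence would not remove it. A reader might also infer that the primary result is compromised. The SPPB is a performance test with assessors stated as blinded. Knowing the arm can influence effort on such a test, but nothing in the documents shows that the primary comparison fails for this reason.

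**Conclusion.** The point holds as a misstatement of who is masked. The protocol twice says that patients or families are not told their group, contradicts this in its blinding section, and describes an intervention that participants and caregivers cannot fail to recognise. The correct description is that outcome assessors are blinded and participants, caregivers and training staff are not.

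Its size is limited. No sample size, analysis model or primary endpoint changes. What changes is how participant-reported secondary outcomes may be interpreted: at least EQ-5D, the depression scale, pain and self-reported adverse events.

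The conclusion assumes that no sham or attention control exists beyond what the article describes, and that EQ-5D, the depression scale and the pain scale are answered by participants in the ordinary way. It needs no assumption about where the exercises are done, which the article does not state.

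**What to change.** Delete or correct the sentence in Study design and setting and in Randomization and blinding. State in its place that participants, caregivers and training staff are not blinded and that only outcome assessors are. Keep the reminder not to disclose the assignment to assessors, and word it so that it plainly assumes participants know their group. Interpret and report participant-reported outcomes (at least EQ-5D, the depression scale, pain and self-reported adverse events) as unblinded.

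The cost is wording and a less favourable description of blinding. The participant information is not shown. If it repeats the sentence it would need changing too, and Trial status says recruitment began in September 2017 and is still open, so that change would come mid-trial. No change to the design, sample size or analysis follows.
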